**Methods:**

People with a diagnosis of pharmacoresistant epilepsy will be recruited in London, United Kingdom, and Freiburg, Germany. Participants will be asked to wear a wrist-worn device and download ad hoc apps developed on their smartphones. The apps will be used to collect data related to sleep, physical activity, stress, mood, social interaction, speech patterns, and cognitive function, both passively from existing smartphone sensors (passive remote measurement technology [pRMT]) and actively via questionnaires, tasks, and assessments (active remote measurement technology [aRMT]). Data will be collected continuously for 6 months and streamed to the Remote Assessment of Disease and Relapse-base (RADAR-base) server.

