### Study Outcomes

The primary outcome of interest was participants’ acceptability and usability of the RADAR technology, including the wearable, the apps, and the assessment scheme. Acceptability and usability will be evaluated using the Post-Study System Usability Questionnaire (PSSUQ) [46]; the Technology Assessment Model Fast Form (TAM-FF) [47]; and ad hoc created qualitative interviews undertaken at 1, 3, and 6 months postenrollment. Participants who dropped out before the study endpoint will be contacted to complete an interview.

Secondary outcomes include (1) sensitivity and false alarm rate of the device, as compared with patient seizure diary, for different seizure types: generalized tonic-clonic seizures, focal seizures (FS) with motor features, FS with autonomic features, and FS with dyscognitive features and (2) identification of variables influencing the long-term trajectory of seizure frequency: pRMT features (measured through the wearable sensors and smartphone sensors), and aRMT assessments, including comorbidities, seizure precipitants, ESM, speech, and cognitive functions.

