### Contextual Variables

Variation in self-esteem will be measured using the Rosenberg Self-Esteem Scale [48], a 10-item self-reported questionnaire. QoL or disability will be measured using the Work and Social Adjustment Scale [49], a 5-item assessment of perceived social and work-related functional impairment used widely across a range of mental and physical disorders. Illness perceptions will be assessed using the Brief Illness Perceptions Questionnaire [50], which provides an insight into participants’ views about their underlying conditions, including a measure of how well they see themselves coping with its symptoms and treatments.

We will seek to identify major changes in participants’ circumstances that may materially affect participants’ outcomes and may also impact the use of RMT. In particular, we will collect information about change in medications for epilepsy, health service utilization (the modified Client Service Receipt Inventory [CSRI]) [51], and change in life circumstances (List of Threatening Experiences Questionnaire [LTE-Q]) [52].

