### Statistical Analysis Plan

Descriptive statistics for demographics, attrition rate, and number of participants using remote assessment measurements will be estimated. The primary outcome measurement (PSSUQ and TAM-FF) will be analyzed using a mixed-effect model for repeated measures based on observed case data. The model will include the duration in the study and contextual variables (CSRI, LTE-Q, etc) as covariates. Using classification approaches, we will investigate whether any demographics and/or other numerical information might serve as a predictor for subjects dropout. Using mixed-effect models with participants as a random factor, we will estimate whether there is a univariate relationship between the amount of RMT usable data during the weeks before the outcome assessment and obtained scale measurements (PSSUQ and TAM-FF). Acoustic features such as pitch, jitter, shimmer, formants, and intensity of the voice will be extracted from the speech task and will be analyzed.

To assess seizure detection performance of a multiparametric wearable system, we will relate seizures detected by the wearable system to the information from the seizure diary, kept by each participant. We will estimate the sensitivity of seizure detection by the wearable system (ie, whether all seizures reported in the diary were detected by wearable system) and false alarm rate (ie, number of seizures detected by the wearable system but not reported in the diary per unit of time, eg, day).

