We will develop an analysis strategy for managing multi-sensor data. To this end, we will investigate what type of features derived from the pRMT and aRMT correlate with seizure occurrence and frequency per unit of time (eg, day and week). Seizure occurrence and frequency will be derived from the multiparametric wearable system and from seizure diaries and analyzed separately. Data obtained from wearable biosensors will be used to derive information about participants’ activity during the day and information about sleep and mood. Aggregated features obtained from biosensors, smartphones, and cognitive tests and from ESM and their changes from baseline or previous time points (delta features) will be used for statistical analysis. First, we will use a univariate approach, where the number of seizures per unit of time will be modeled with each variable or feature as a fixed effect and participant as a random effect. Demographics and other baseline characteristics will be added to the model when necessary. Correction for multiple comparisons will be taken into account. Second, using aggregated data obtained through some time duration to predict the number of seizures per the same time duration, we will construct predictive models. Under the assumption that data are missing at random, multiple imputation will be applied for covariates, where missingness is not drastically high. Multivariate prediction models will be constructed, and variable selection, based on, for example, least absolute shrinkage and selection operator L1-regularization for linear models, or different feature selection algorithms will be applied. Model performance will be characterized through cross-validation, putting stress on the sensitivity and specificity of the predictive model.

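### The stated primary, usable-data and univariate seizure models do not name site, which fixes language and country, so a covariate's coefficient could absorb a site difference

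*Protocol article*

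**What the plan says.** All of the following is in the Protocol article.

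- **Sites and language.** The abstract's Methods state: "People with a diagnosis of pharmacoresistant epilepsy will be recruited in London, United Kingdom, and Freiburg, Germany". The inclusion criteria require fluency and literacy in English, or in German at Freiburg. Site therefore determines both language and country.
- **Primary model.** Under Statistical Analysis Plan, PSSUQ and TAM-FF "will be analyzed using a mixed-effect model for repeated measures based on observed case data", and then: "The model will include the duration in the study and contextual variables (CSRI, LTE-Q, etc) as covariates". The section Contextual Variables says what that class holds: self-esteem, work and social adjustment, illness perceptions, medication changes, use of health services (CSRI) and life events (LTE-Q). Site is not among them.
- **Usable-data model.** The relation between the amount of usable data and the two scales is described as univariate, with participant as a random factor.
- **Seizure models.** In the first step, "the number of seizures per unit of time will be modeled with each variable or feature as a fixed effect and participant as a random" term. Then: "Demographics and other baseline characteristics will be added to the model when necessary".
- **Speech.** Study Outcomes lists, among the candidate influences on seizure frequency, "aRMT assessments, including comorbidities, seizure precipitants, ESM, speech, and cognitive functions". The Statistical Analysis Plan adds: "Acoustic features such as pitch, jitter, shimmer, formants, and intensity of the voice will be extracted from the speech task". It says that these will be analysed, but not in which model.
- **Form of the features.** Both aggregated levels and changes from baseline or from the previous time point (delta features) are planned.

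**The concern.** The article gives concrete model structures, and the one stratum built into the design is in none of them. Several model variables could plausibly differ between the sites. Service use is recorded in two countries. Questionnaires are answered in two languages. Free speech is recorded in two languages and scored automatically for sentiment. Participants come from differently organised departments, so case mix could differ too.

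If an outcome also differs by site, a model without site credits part of that difference to whichever covariate differs along with it. A difference between centres in usability ratings could then appear as an association with service use. A difference between centres in seizure frequency could appear as a speech marker of seizures. A participant random intercept looks like protection but is not. It models the correlation within a person, and it assumes that the person effects are unrelated to the covariate. That assumption fails when both depend on site.

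**Working it through.** **No figure to reproduce.** The article states no alpha, power, SD or effect size for these models, and gives no calculation behind the 32. The check is therefore a reading of the text plus an illustration of the mechanism.

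**Text check.** Site, country and language are named in no model. The primary covariate list is open-ended, but the open bracket expands a class that Contextual Variables defines without site.

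**Inputs from the article:** 32 participants, two sites, outcome visits at 1, 3 and 6 months.

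**Assumed inputs:**
- share at one site p = 0.5, with 0.75 as an alternative;
- site differences dx (covariate) and dy (outcome), in within-site SDs;
- no association within site, and a two-sided 5% test.

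**Size of the bias.** With x = dx·s + e and y = dy·s + f, where s is the site indicator and e and f are independent with unit variance:

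pooled slope = cov(x, y) / var(x) = dx·dy·p(1−p) / [1 + dx²·p(1−p)]

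At p = 0.5, p(1−p) = 0.25:
- dx = dy = 0.5: 0.0625 / 1.0625 = 0.06
- dx = 1, dy = 0.5: 0.125 / 1.25 = 0.10
- dx = dy = 1: 0.25 / 1.25 = 0.20
- dx = 2, dy = 1: 0.5 / 2 = 0.25

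**Person-level regression, N = 32, 2,000 runs per setting, p = 0.5**

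| dx | dy | False positives without site | With site |
|---|---|---|---|
| 0 | 0.5 | 5.5% | 5.1% |
| 0.5 | 0.5 | 5.2% | 4.2% |
| 1 | 0.5 | 9.8% | 5.4% |
| 1 | 1 | 20.9% | 5.2% |
| 2 | 1 | 46.6% | 5.0% |

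At p = 0.75 the last two rows give 14.9% and 31.0% without site.

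**Random-intercept model, N = 32, three visits, 16 per site, 250 runs per setting.** The assumed intraclass correlations are 0.6 for the outcome and 0.7 for the covariate.

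| dx | dy | Mean slope without site | False positives without site | With site | Delta covariate, no site |
|---|---|---|---|---|---|
| 0.5 | 0.5 | 0.03 | 8.0% | 5.2% | 4.4% |
| 1 | 1 | 0.10 | 16.0% | 2.8% | 5.6% |
| 2 | 1 | 0.16 | 39.2% | 6.4% | 6.4% |

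With site in the model, the mean slopes are within 0.004 of zero.

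**Precision.** With 250 runs, the Monte Carlo standard error is √(0.16 × 0.84 / 250) = 2.3 points at 16%, √(0.08 × 0.92 / 250) = 1.7 points at 8%, and √(0.05 × 0.95 / 250) = 1.4 points at 5%. The 8% is thus not clearly separate from 5%, while the 16% and 39% are. The outcome was simulated as normal, so for seizure counts the mechanism carries over but the exact rates do not.

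**Reading the results.** Inflation needs a site difference in both covariate and outcome, and it is small when either is small. The random intercept does not remove it. A site term does. A delta covariate largely escapes it, because subtraction removes a stable site offset.

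**The case against.** The strongest reply is that this is silence, not error. A journal article condenses a fuller plan, which may name site. The primary covariate list is left open, and the seizure models allow baseline characteristics where needed. Part of this stands: site is unnamed, not excluded, and the seizure wording would permit it. But the primary list expands a class that the article itself defines without site, and the usable-data model is called univariate. A fuller plan that names site would have to be reconciled with both.

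A reader might infer that service use and speech features are in fact confounded with country. The article does not support that. It reports no site difference in PSSUQ, TAM-FF, CSRI, speech or seizure rate and no split by site, and it applies the same minimum seizure frequency at both centres. That health systems affect CSRI is inferred from the countries.

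Nor should the figures be read as bias in the primary usability result. They concern a covariate's coefficient, and the article states no hypothesis about service use and usability.

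On speech, several limits stand:
- The list of aggregated features for the seizure analysis does not name it. It enters through Study Outcomes and the general reference to active-measurement features.
- The reading text is described as phonetically balanced in different languages, although that does not cover the free-response question or the sentiment scores.
- A correction for multiple comparisons is planned, so single-test rates at 5% overstate what would be declared significant. The correction does not remove bias in the slope.

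**Conclusion.** The point holds as a specification weakness of moderate weight. The stated primary, usable-data and univariate seizure models do not name site, site fully determines language and country, and a participant random effect does not protect raw-level covariates from a between-site difference.

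It is a risk, not a demonstrated bias. Its size rests on assumed site differences and, for most results, an assumed equal split. The false positive rate is about 5-8% at 0.5 SD in both covariate and outcome, and about 16-21% at 1 SD each with 16 per site. With site included it is about 3-6%. Delta features are largely unaffected. If the sites do not differ, omitting site causes no such bias.

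**What to change.** 1. Name site (equivalently, language) as a fixed effect in the primary PSSUQ and TAM-FF model, the usable-data model and the univariate seizure models. With only two sites, a random site effect could not be estimated in practice.
2. Standardise raw-level speech and sentiment features within language before pooling. In the univariate models this overlaps with the site term for mean shifts, but it also handles a difference in spread.
3. Show the primary scale means by site.

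The cost is a few sentences of wording and one degree of freedom per model, with no change to data collection. A site term in the LASSO and cross-validated prediction models is optional and not part of this fix, because a site indicator there may not carry over to new centres.

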## Methods

### Study Design and Population

This study is a multicenter, prospective, observational, nonrandomized, and noninterventional cohort study in which 32 individuals with a diagnosis of epilepsy will be asked to download several RMT apps and use a wearable device for up to 6 months of follow-up. The inclusion and exclusion criteria are provided in Textboxes 1 and 2, respectively.

Inclusion criteria.Inclusion criteriaAble to give informed consent for participationDiagnosis of epilepsyAged between 18 and 70 yearsMinimum average seizure frequency of 2 seizures per monthWilling and able to complete self-reported assessments via smartphonesFluent in English (German in Freiburg) and able to read and write English (German in Freiburg)Willing to continuously wear the study wearable deviceExisting ownership of an Android smartphone (or willingness to use an Android smartphone, which will be provided as their only smartphone)Existing ownership or the possibility of connecting to a Wi-Fi connection on a daily basis

Exclusion criteria.Exclusion criteriaEstablished diagnosis of psychogenic nonepileptic attacks (dissociative seizures) as the only seizure typeFrequent vigorous involuntary movements (eg, chorea and athetosis) or frequent parasomnias with major motor components (eg, sleep walking and night terrors)Inability to comply with the trial procedure, such as cognitive or behavioral problemsInability to give informed consentUnwillingness to use an Android smartphone

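### The model relating usable RMT data to PSSUQ and TAM-FF has no time term, so it cannot separate drift over follow-up from a link between use and usability

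*Protocol article*

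**What the plan says.** The Statistical Analysis Plan section describes two separate models for the usability and acceptability scales.

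- **Primary model.** PSSUQ and TAM-FF are analysed with a "mixed-effect model for repeated measures based on observed case data". For this model the plan adds: "The model will include the duration in the study and contextual variables (CSRI, LTE-Q, etc) as covariates".
- **Use-and-rating model.** The plan introduces this second model with the words "Using mixed-effect models with participants as a random factor". Its target is the "univariate relationship between the amount of RMT usable data during the weeks before the outcome assessment and obtained scale measurements". No other term is named. The length of the window is not given, nor whether the amount is a total or a share of possible time.

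Table 1 schedules both scales at weeks 4, 12 and 24. Study Outcomes gives the matching times for the evaluation as "undertaken at 1, 3, and 6 months postenrollment". The abstract says of the RMT data: "Data will be collected continuously for 6 months". The planned sample is 32 participants.

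**The concern.** The second model is the only analysis the article describes that links actual use of the technology to the scales measuring the primary outcome. It has one predictor and a participant effect, so any trend over time that the amount of data and the ratings share is credited to the amount.

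Such trends are plausible by the protocol's own account. The primary model treats time in study as relevant to these scores. The Study Monitoring section foresees changes to software and questionnaire schedule during the study to improve usability, and telephone calls to support adherence. Ratings and data yield may therefore both move during follow-up.

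At stake is the reading of the result. A novelty or fatigue effect could be reported as an association between use and usability. Its sign would depend on the window. If interval totals grow while ratings worsen, more use appears to go with worse usability. If wear falls over a fixed window while ratings worsen, more use appears to go with better usability.

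**Working it through.** The documents state no significance level, effect size or SD for this analysis, so there is no figure of the plan to reproduce.

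**1. Intervals (Table 1).** The weeks before each rating are 4 - 0 = 4, 12 - 4 = 8 and 24 - 12 = 12. Counted from enrolment they are 4, 12 and 24. Interval length correlates 0.99 with study week.

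**2. Inputs.** From the documents: 32 participants and 3 ratings each, so at most 32 x 3 = 96 ratings per scale. Assumed: two-sided 5% level; rating SD 1; within-person correlation 0.5; mean usable fraction 0.70, with between-person SD 0.20 and within-person SD 0.10, truncated to 0.02-1; complete data; linear drift *d* (in SD) from week 4 to week 24.

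**3. Data generated with no link between use and rating.**

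- Rating: y_ij = u_i + e_ij + d(w_j - 4)/20, with w = 4, 12, 24 and Var(u) = Var(e) = 0.5. For d = 0.5 the mean shifts are 0, 0.5 x 8/20 = 0.20 and 0.5 x 20/20 = 0.50.
- Amount: a_ij = f_ij x g_j, where f is the usable fraction (independent of the rating) and g = 4, 8, 12 for interval totals, or 4, 4, 4 for a fixed window. Cumulative totals sum the interval amounts.

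**4. How far the amount marks the visit.** Mean interval totals are 2.76, 5.52 and 8.28 usable weeks. The variance of these three means is 2 x 2.76²/3 = 5.08. That is about 62% of the total variance of the amount.

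**5. Model fitted.** y_ij = b0 + b1·a_ij + u_i + e_ij, random intercept by REML; reject if |b1/SE| > 1.96. There were 1,500 runs per cell, so the Monte Carlo SE at 5% is √(0.05 x 0.95/1500) = 0.006.

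| Drift (SD) | Interval total | Cumulative total | Fixed 4 weeks, stable wear | Fixed 4 weeks, wear falling 10 then 20 points |
|---|---|---|---|---|
| 0 | 0.05 | 0.05 | 0.06 | 0.06 |
| 0.2 | 0.18 | 0.21 | 0.07 | 0.10 |
| 0.3 | 0.33 | 0.37 | 0.05 | 0.15 |
| 0.5 | 0.72 | 0.75 | 0.05 | 0.31 |
| 0.8 | 0.98 | 0.98 | 0.07 | 0.59 |

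**6. With visit added as a categorical effect.** Interval total: 0.06-0.07 at every drift. Fixed window with falling wear: 0.05-0.06 at every drift.

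**7. Sensitivity.** For the interval total at 0.5 SD drift, rejection is 0.55 with within-person correlation 0.3 and 0.91 with 0.7. A separate simulation (mean wear 75%, 1,000 runs per setting) gave, for drifts of 0.3 and 0.5 SD:

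- interval total: 34% and 72%;
- cumulative total: 35% and 76%;
- interval or cumulative totals with wear falling 30 points: 18-26% and 40-63%;
- fixed 4-week window with wear falling 30 points: 23% and 53%;
- visit in the model: 4.5-6.1% in every case.

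**The case against.** The strongest reply is that the growing window is not in the text. The plan speaks only of weeks before the assessment, and a fixed number of weeks fits that wording equally well. Elsewhere the same section counts false alarms and seizures per unit of time. A condensed article may leave window and unit to a fuller document. This stands: the 33-34% and 72% apply to one reading only, and the undefined window is not itself the finding.

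A reader might go further and infer that the test rejects for any drift, and that it detects time rather than use. The documents do not support that. With a fixed window and stable wear the written model holds about 5-7%. Even with interval totals, a drift of 0.2 SD gives 18%. Differences in use between participants still contribute, so a true link would register, though mixed with time. Nor is the primary analysis undermined, since it adjusts for time in study.

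It can also be said that the analysis is exploratory, with no stated hypothesis or level, and that a joint decline in wear and ratings may interest a feasibility study. Both points are fair. They limit the weight of the concern, but such a joint decline would still not show that use and usability are linked at a given time.

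Finally, univariate may mean one feature at a time, as in the seizure models, where baseline characteristics may be added. That allowance is written for the seizure models and for baseline characteristics, not for time in this model.

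The missing time term is therefore a stated modelling choice. It matters under either reading of the window when wear and ratings both change.

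**Conclusion.** The point holds in conditional form. As written, the model cannot separate drift over follow-up from a link between use and usability.

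- **Interval totals:** false-positive rate about 33-34% at 0.3 SD drift and 72% at 0.5 SD.
- **Fixed 4-week window, wear falling 20 points by the last visit:** about 15% and 31%.
- **Fixed window with stable wear, or no drift in ratings:** no material inflation.

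The drift, wear and correlation values, the 5% level and the absence of dropout are all assumptions; the documents supply none of them. The schedule, the sample size and the lack of a named time term come from the article. This is a secondary, exploratory analysis and the primary model is unaffected, so the change is worth making but not critical.

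**What to change.** In the Statistical Analysis Plan section, make two changes to the sentence on usable data and scale scores.

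1. Add visit (week 4, 12, 24) as a categorical fixed effect. This does the main work: it brings the rate back to about 5-7% under both the growing and the fixed window.
2. State the window and express the amount as a proportion of possible recording time within it, so that one unit means the same at each visit. With the assumed between-person SD of 0.20, the spread of a total would rise from 0.20 x 4 = 0.8 weeks at the first rating to 0.20 x 12 = 2.4 weeks at the last. A common 4-week window is one option, being the longest available within the interval before all three ratings. A proportion over the whole interval is another.

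The second change alone is not enough if wear falls over follow-up. The visit term removes the time trend shared by all participants, not trends peculiar to individuals.

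The cost is two degrees of freedom, a sentence of wording and no new data. If the 4-week window is chosen, 12 - 4 = 8 of the 12 weeks before the last rating are not counted.

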## Abstract

**Background:**

In recent years, a growing body of literature has highlighted the role of wearable and mobile remote measurement technology (RMT) applied to seizure detection in hospital settings, whereas more limited evidence has been produced in the community setting. In clinical practice, seizure assessment typically relies on self-report, which is known to be highly unreliable. Moreover, most people with epilepsy self-identify factors that lead to increased seizure likelihood, including mood, behavior, sleep pattern, and cognitive alterations, all of which are amenable to measurement via multiparametric RMT.

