## Introduction

### Background

The last decade has seen an explosion in the capability of monitoring individuals via sensors in smartphones or wearable devices, and the range of parameters that can be measured by such technologies will continue to grow [1]. Remote measurement technologies (RMTs) can unobtrusively measure human behavior and physiology and, combined with active measurement of daily experiences via smartphone apps, is an innovation that could be used to provide real-time information about the current clinical state of patients and information potentially predictive of future deterioration [1]. RMT appears to be particularly interesting for those chronic conditions whose course is dynamic and characterized by multiple variations in parameters that can be measured remotely, actively and/or passively [2,3]. Epilepsy is one of the most common neurological disorders, affecting approximately 0.6% of the population worldwide [4]. It is characterized by recurrent seizures that manifest with physiological and behavioral phenomena [5]. Seizures are mostly unprovoked and unpredictable, and about 1 in 3 of all people with epilepsy do not respond to any medication and continue to have uncontrolled seizures [6]. The personal, social, and economic costs of uncontrolled epilepsy are considerable: seizure recurrence and unpredictability worsen the quality of life (QoL) of people with epilepsy and their families [7], people with active epilepsy have 4 to 5 times higher standardized mortality ratios compared with seizure-free individuals [8-12], and the economic burden for the health system is significant across countries [13,14]. Despite new antiepileptic drugs coming to the market, there is limited evidence of a substantial difference to treatment-refractory patients [15], and overall, the mortality associated with epilepsy has not decreased in the last 50 years [16]. One reason for the failure of trials of new treatments is that it is difficult to collect objective data regarding relevant clinical outcomes (eg, number of seizures and response to treatment) and that subjective patient and family recall and reporting is of limited utility and largely unreliable [17]. Similarly, an objective and continuous collection of information on seizure occurrence, frequency, and distribution would guide a more tailored management and inform decisions on treatment optimization in the clinical setting. In the diagnostic setting, the gold standard for seizure detection is electroencephalography (EEG) in combination with video monitoring. This method has, by definition, a high sensitivity and a positive predictive value close to 100%. However, video EEG monitoring is not a practical procedure for long-term seizure tracking for different reasons: it cannot be implemented for more than a few days at a time, wearing EEG electrodes is uncomfortable and potentially stigmatizing for the patient, EEG requires considerable care by technicians to maintain a high signal quality, and analysis of videos and EEG signals are time consuming and costly [18].

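### The wearable's false alarm rate counts true seizures missing from the diary as errors, so it is biased upward and should be reported as disagreement with the diary

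*Protocol article*

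**What the plan says.** The Study Outcomes section of the protocol article lists as a secondary outcome the "sensitivity and false alarm rate of the device, as compared with patient seizure diary, for different seizure types", and names four types, one of them "FS with dyscognitive features". The Statistical Analysis Plan section then fixes both measures. Sensitivity asks "whether all seizures reported in the diary were detected by wearable system". The false alarm rate is the "number of seizures detected by the wearable system but not reported in the diary per unit of time", with the day as an example of the unit.

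Under Study Technology, the diary is self-report. An app prompt each evening asks about seizures, and a participant who reports one is taken to a diary covering time, manifestations and possible precipitants.

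On self-report in general, the Abstract says that "seizure assessment typically relies on self-report, which is known to be highly unreliable", and the Background of the Introduction says that "subjective patient and family recall and reporting is of limited utility and largely unreliable". That Background also states that "the gold standard for seizure detection is electroencephalography (EEG) in combination with video monitoring", and explains why it is impractical for long-term tracking. For the detection analysis the article describes no adjudication, witness confirmation, video-EEG subset or allowance for unreported seizures. The second aim under Study Objectives is more modest: it asks for the correspondence between patient-marked events and the passive data.

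**The concern.** A false alarm is a detection when no seizure occurred. The plan counts something else: a detection when no seizure was written down. The two differ by every true seizure that the wearable picks up and the participant does not report. The article gives reason to expect such seizures. It calls self-report unreliable, and it includes dyscognitive focal seizures, of which the person may plausibly be unaware. Under this definition, a device that finds more of what participants miss scores worse.

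At stake is what the study may conclude about detection accuracy. The Principal Findings section says that false alarms can increase distress and harm acceptance and long-term use, so a rate published under that name will be read as a property of the device. The definition is fixed in the article itself and is not a detail left to a separate document.

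There is also a practical gap. Study Outcomes asks for both measures by seizure type, but a detection without a diary entry has no diary-based type.

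**Working it through.** The article states no sensitivity, false alarm rate or diary accuracy, so there is no figure to reproduce. The check shows the direction of the bias and its size over assumed values.

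**Inputs from the article:** 32 participants, up to 6 months, and a minimum average of 2 seizures per month. That is 32 × 6 = 192 participant-months and 192 × 2 = 384 seizures at the minimum.

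**Assumptions:** diary completeness *c* (the share of true seizures entered), the wearable's detection probability for unreported seizures *d*, no genuine false alarms, and 30.4 days per month.

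**False alarm rate.** With true seizure rate λ,

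excess per month = *d* × (1 − *c*) × λ.

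This is never negative, so unreported seizures can only raise the rate. With λ = 2 per month and *d* = 0.9:

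| *c* | excess per month | per day | over 192 participant-months |
|---|---|---|---|
| 0.9 | 0.18 | 0.006 | 35 |
| 0.7 | 0.54 | 0.018 | 104 |
| 0.5 | 0.90 | 0.030 | 173 |
| 0.3 | 1.26 | 0.041 | 242 |

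With perfect detection (*d* = 1) and *c* = 0.5, the total is 0.5 × 384 = 192, so even a perfect device shows a rate above zero. If 2 per month is the reported rate, the true rate at *c* = 0.5 is 4, and the excess with *d* = 0.9 is 1.8 per month, or 0.059 per day.

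At 10 reported seizures per month and *c* = 0.5, the true rate is 20 and 10 go unreported. The result then depends on *d*:

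- If unreported seizures are detected as well as any other (*d* = 0.9): 10 × 0.9 = 9 per month, and 9 / 30.4 = 0.30 per day.
- If unreported seizures are mostly of a kind the wearable detects poorly: take 20% convulsive (90% reported, 90% detected) and 80% focal (40% reported, 20% detected). Completeness is again 0.2 × 0.9 + 0.8 × 0.4 = 0.50. Unreported but detected seizures are 20 × (0.2 × 0.1 × 0.9 + 0.8 × 0.6 × 0.2) = 20 × 0.114 = 2.28 per month, or 0.075 per day.

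**Sensitivity.** With true sensitivity *s* and reporting probabilities *r1* for detected and *r0* for undetected seizures,

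diary-based sensitivity = *s r1* / (*s r1* + (1 − *s*) *r0*).

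For *s* = 0.6:

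- *r1* = *r0*: 0.60, no bias.
- *r1* = 0.9, *r0* = 0.4: 0.54 / (0.54 + 0.16) = 0.77.
- *r1* = 0.4, *r0* = 0.9: 0.24 / (0.24 + 0.36) = 0.40.

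If a share *q* of diary entries are not seizures and match no detection, the value becomes *s*(1 − *q*). For *s* = 0.9 and *q* from 10% to 30%, that is 0.81 to 0.63.

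**The case against.** - **The comparator is disclosed.** Study Outcomes names the diary, and the Statistical Analysis Plan section spells out both definitions. This stands, and it makes the remedy mainly one of labelling. But disclosure does not turn an unreported seizure into a false alarm, and the article nowhere limits the interpretation.
- **The remarks on unreliability are about something else.** The Abstract speaks of routine practice and the Introduction of patient and family recall, whereas the study uses a daily prompt with event times. This partly stands: the diary may well be better than clinic recall. It does not help where the person was unaware of the seizure.
- **Video-EEG for six months is impractical.** This stands and explains the choice of a diary. It does not validate the label.
- **Device-derived and diary-derived seizure counts are analysed separately.** That applies to the feature and frequency models. The detection definitions are unchanged by it.
- **Selective reporting of convulsive seizures.** A reader might infer that sensitivity must be overstated because convulsive seizures are both better reported and better detected. In the mixed scenario above, pooling types does give (0.18 × 0.9 + 0.32 × 0.2) / 0.50 = 45% against a true 0.2 × 0.9 + 0.8 × 0.2 = 34%. But Study Outcomes plans sensitivity by seizure type, and the same inputs then give 90% and 20%, both correct. Only selection within a type could remain, and its direction is unknown.
- **Dissociative seizures.** Only an established diagnosis of "psychogenic nonepileptic attacks (dissociative seizures) as the only seizure" type is excluded, so a reader might infer that dissociative events will fill the diary with missed seizures. The article gives no prevalence, takes a medical history at baseline, records manifestations in the diary and restricts the outcome to named epileptic types. This is a supporting point only.

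**Conclusion.** The concern holds for the false alarm rate. As defined, it is biased upward by every true, detected but unreported seizure. The direction is certain; the size is not. At 50% completeness, the excess is about 0.03 per day at a true rate of 2 per month with 90% detection, and about 0.08 to 0.30 per day at 10 reported seizures per month. The upper end should not be taken as the expected value: it needs five times the entry minimum, and unreported seizures as detectable as reported ones. Completeness and detection are assumptions throughout.

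For sensitivity the claim is weaker. Within a seizure type it is unbiased if reporting is independent of detection and every entry is a true seizure. Otherwise the bias can go either way.

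This should be fixed, but it is not a fatal flaw. The outcome is secondary, and the primary outcome (acceptability and usability, by questionnaires and interviews) is unaffected.

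**What to change.** Change Study Outcomes and the Statistical Analysis Plan section to match the correspondence aim:

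1. Report, by seizure type, the percentage of diary-reported seizures with a matched device detection.
2. Report device detections without a diary entry per recorded day, overall and not by type.
3. State that the second measure is an upper bound on the false alarm rate and not an estimate of it, apart from genuine false alarms that match a diary entry by chance.
4. Add a table of the implied false alarm rate over assumed completeness *c* (for example 30%, 50%, 70% and 90%) and detection of unreported seizures *d*. If every diary entry is a true seizure, the implied rate is the observed device-only rate minus *d* × reported seizure rate × (1 − *c*) / *c*. A negative value shows that the assumed pair does not fit the data.
5. Optionally, use the baseline medical history to flag participants with coexisting dissociative seizures and repeat the analysis without them.

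The cost is rewording in two sections and one table. Design and sample size are unchanged, and the optional step uses history already scheduled. The study gives up an unqualified claim about sensitivity and false alarms.
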